### Sample size calculations

The number of participants required for this study is based on power calculations for the expected changes in total body lean mass, lower limb muscle strength and cognitive function, particularly executive function. Based on our previous study in elderly women [15], we estimate that 152 older adults in each group will provide >80 % power (P<0.05, two tailed) to detect a 0.5 kg and 18 % differences for the change in total body lean mass and leg muscle strength between the red meat and control group, assuming a standard deviation of 0.9 kg and 30 %, respectively. This calculation allows for a possible 20 % drop-out or loss to follow-up. For measures of cognitive function, it was difficult to provide an accurate estimate of the magnitude of any intervention effect (effect size) because this study is the first to examine the effects of exercise combined with increased dietary protein compared to exercise alone in older adults. Previous research examining the effects of exercise on measures of cognitive function report moderate effect sizes (*d* = 0.41 to 0.59) following PRT or aerobic training alone or in combination [25, 26, 73], particularly on measures of executive function and processing speed. Whether increased dietary protein can improve cognitive function in older adults remains uncertain, but we hypothesize that exercise combined with a modest increase in dietary protein (1.3 g/kg/day) will lead to a medium effect. Using data from a pilot study in 72 healthy older adults aged 65 years and over in which the mean (standard deviation, SD) scores on the CogState Groton Maze Learning Task (a measure of executive function) and the Detection Task (a measure of reaction time and processing speed) were 64 (18) and 2.56 (0.07) respectively, we anticipate that a sample size of at least 140 will provide approximately 80 % power (P<0.05, two-tailed) to determine a medium effect size (*f* = 0.20) assuming a 0.6 correlation among repeated measures.

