##### Cognitive function

The CogState Brief Battery computerized tests (http://cogstate.com/) will be used to assess cognitive function at baseline, 12 and 24 weeks. Briefly, this is a multi-task computerised battery which provides sensitive and valid measurement of a range of different cognitive functions [53–55], including attention, processing speed, memory and executive function. It is designed to assess cognition over serial time points using a computerised system that takes 30–40 minutes to complete depending on the number of tests used. Importantly, it has been specifically designed for repeated administration over short time periods and has been validated in older adults, with minimal practice or fatigue effects, making it suited for detecting subtle change [53–55]. For this study, participants will be asked to complete five tasks from the CogState battery on a laptop with a mouse and headphones provided. Prior to each test, participants will be given a verbal set of instructions, reinforcing the instructions written on the screen. Participants will also be given a practice to ensure that they understand what is required for each test. A brief description of the five tasks is provided below.The *Groton Maze Learning Task (GMLT)* is a test of executive function, memory and spatial problem solving. In this test, participants will be exposed to a 10 x 10 grid of tiles on a computer screen, with a 28-step pathway hidden among the 100 possible locations. Participants will be required to find the hidden pathway (through trial and error feedback) that extends from one corner of the grid to the other, and remember (repeat) this pathway for four subsequent trials. The task is scored using the total number of errors made by the participant on five consecutive trials at a single session. The lower the score, the better their performance.The *Detection Task (DET)* is a test of reaction time measuring psychomotor function and speed of processing. In this task, participants will be shown the back of a playing card (patterned side) in the centre of the screen and asked to respond to the question “has the card turned over yet? As soon as the card is flipped to the picture side, participants will be required to press ‘yes’ on the keyboard as quickly as possible. The task is completed after 35 correct trials have been recorded. This task is scored using speed in milliseconds. The average reaction times for correct responses will be used, normalised using a log10 transformation.The *Identification Task (IDN)* is a test of choice reaction time measuring visual attention. For this task, participants will be shown the back of a playing card in the centre of the screen, and asked to respond to the question ‘is the card red?” As soon as the card is flipped to the picture side, the participants have to decide as quickly as possible whether the card is red or black. If the card is red, participants will press the ‘yes’ key. If the card is black, they will press the ‘no’ key. The task will end after 30 correct responses have been recorded. The task is scored using speed in milliseconds and mean reaction times for correct responses. The average will be normalised using a log10 transformation.The *One Card Learning Task (OCLT)* is a test assessing visual recognition memory and attention. In this task, participants will be shown the back of a playing card in the centre of the screen and asked to respond to the question “have you seen this card before in this task?” If the participant has seen the card, they will be required to press the ‘yes’ key, or the ‘no’ keys if they have not. In this task, six cards are randomly drawn from the deck and repeated throughout the task, and the first response will always be ‘no’, as there has been no previous card shown to the participant in the task. This task will end after 88 trials, and is scored using the proportion of correct responses, using an arcsine square-root transformation to normalise the data.The *One-Back Working Memory Task (OBWMT)* is a test assessing working memory and attention. In this task participants will be shown the back of a playing card in the centre of the screen, and asked to respond to the question “is this card the same as that on the immediately previous trial?” If the answer is yes participants will be required to press the ‘yes’ key, or the ‘no’ key if the card is not the same. The first response in this task is always ‘no’ as there is no card prior to the first card. The task will end after 30 correct responses have been recorded. This test is scored using the proportion of correct responses, using an arcsine square-root transformation to normalise the data.

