### Statistical analyses

The primary statistical analysis will be conducted on an intention-to-treat basis using STATA statistical software release 13.0 (STATA, College Station, TX, USA). For participants with at least 66 % compliance to the exercise program (two out of three sessions per week) and 80 % compliance with the lean red meat, per protocol analyses will also be performed. Descriptive statistics will be used to compare the background variables and baseline measures between the groups, and any imbalances will be adjusted for during subsequent analyses. Wherever possible, we will obtain endpoint measures from all withdrawals and include all randomised participants in our final data analysis. Any missing data for participants that are lost to follow-up will be handled with multiple imputation, but sensitivity analysis will be conducted to evaluate the effect of potential non-random attrition. All data will be checked for normality prior to analysis, and data that is skewed will be log transformed prior to analysis. Baseline measures and changes in outcome variables will be presented as means ± SD or 95 % confidence intervals. The effects of the intervention will be assessed using linear mixed models with random effects. Subsequent adjusted analysis for potential covariates (age, sex, race/ethnicity, cardiovascular disease risk, depression/anxiety, changes in medication and change in habitual physical activity or diet) will also be conducted. Multiple regression analysis will be used to investigate whether body composition, circulating neurotrophic, growth or inflammatory markers, bioavailable zinc and cardiovascular risk factors are associated with changes in cognitive function. The significance level will be set at P<0.05 or smaller if adjustments are made for multiple comparisons.

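### The 140 participants stated for cognitive power carry no allowance for the protocol's own 20% drop-out, and the contrast that f = 0.20 describes is not named

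*Protocol article*

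**What the plan says.** The Sample size calculations section treats the endpoints in two steps. The first covers total body lean mass (difference 0.5 kg, SD 0.9 kg) and leg strength (difference 18%, SD 30%). It closes with "This calculation allows for a possible 20 % drop-out or loss to follow-up". The second covers cognitive function: "we anticipate that a sample size of at least 140 will provide approximately 80 % power (P<0.05, two-tailed) to determine a medium effect size", with f = 0.20 and "assuming a 0.6 correlation among repeated measures". No drop-out figure accompanies this second step, and the text does not say whether 140 counts people enrolled or people with data.

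Enrolment is given in two ways. The Abstract (Methods/Design) and the Participants section give 152, or at least 152, in total. The Sample size calculations section gives 152 for each group.

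The Cognitive function section says that the CogState tests "will be used to assess cognitive function at baseline, 12 and 24 weeks". The Primary outcome measures section defines the primary outcomes as changes. The Statistical analyses section says "The effects of the intervention will be assessed using linear mixed models with random effects", without naming the contrast, and adds multiple imputation and an effort to obtain endpoint data from people who withdraw.

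**The concern.** The same participants supply the muscle and the cognitive endpoints. A paragraph that allows for 20% loss on one and is silent on the other is inconsistent unless 140 already means evaluable participants. If it does, the planned total of 152 is too small to deliver them at that rate of loss.

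A second gap makes this hard to settle from the text. An f of 0.20 with a correlation among repeated measures can describe a group effect averaged over visits, a group-by-time effect or a difference in change. These give very different sample sizes, and the paragraph does not say which is meant.

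At stake is how a null cognitive result would be read. Readers would set it against a stated power of about 80%, which under several plausible contrasts the expected number of completers does not provide.

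**Working it through.** **Inputs.** From Sample size calculations: two-sided alpha 0.05, f = 0.20, correlation ρ = 0.6, 20% loss. From Cognitive function: m = 3 visits. From the Abstract and Participants: 152 in total. Assumptions: 1:1 allocation (two groups, blocks of four, no ratio stated) and equal correlation between visits. For two equal groups d = 2f = 0.40, so f² = 0.04 = d²/4.

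**Step 1: reproduce 140.** For the between-group effect of a repeated-measures ANOVA, the noncentrality is λ = f²·N·m / (1 + (m−1)ρ), with 1 and N−2 degrees of freedom.
- N = 140: λ = 0.04 × 140 × 3 / 2.2 = 7.64, power 78.4%.
- N = 146: λ = 7.96, power 80.0%.

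This agrees with the stated figure to within two percentage points. Other readings, as N for 80% power:
- group-by-time with λ = f²·N·m / (1−ρ): 34
- week-24 baseline-adjusted difference: 128
- week-24 change score: 160
- overall group-by-time test with d = 0.40 at weeks 12 and 24 and zero at baseline: 148 (78.2% at 140)

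The between-group formula is therefore the most direct match, but the last reading fits almost equally well.

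**Step 2: apply the drop-out.**
- 152 × 0.8 = 121.6, about 122, which is below 140.
- 140 / 0.8 = 175 enrolled would be needed to keep 140.
- 1 − 140/152 = 7.9% is the largest loss that 152 can absorb.

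**Step 3: power at N = 122.**
- Between-group effect over three visits: λ = 0.04 × 122 × 3 / 2.2 = 6.65, power 72.5%.
- Week-24 change score, variance 2(1−ρ) = 0.8: λ = 4.88 / 0.8 = 6.10, power 68.8%.
- Overall group-by-time, sustained d = 0.40, 2 degrees of freedom: λ = 8.13, power 71.9%.
- Week-24 baseline-adjusted, variance 1−ρ² = 0.64: λ = 4.88 / 0.64 = 7.63, power 78.2%.
- Change to the mean of weeks 12 and 24, variance 0.8 + 1 − 1.2 = 0.6: λ = 8.13 on 1 degree of freedom, power 80.8%.
- Baseline-adjusted mean of weeks 12 and 24, variance 0.8 − 0.36 = 0.44: λ = 11.09, power 91.0%.

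Here 4.88 is 0.04 × 122. For the week-24 baseline-adjusted contrast, the difference detectable with 80% power at 122 is d = 0.41.

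**Step 4: the muscle endpoints for comparison.** At 61 per arm, power is 86.6% for lean mass and 91.2% for strength. A total of 152 with 20% loss supports those claims; the gap concerns cognition alone.

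**Step 5: the other enrolment figure.** Taken literally, 152 per group is 304 in total, and 304 × 0.8 = 243 exceeds 140.

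**The case against.** The strongest reply is that the shortfall depends on a contrast the article does not name and may properly leave to an analysis plan. At 122, the week-24 baseline-adjusted contrast has 78% power, which is fairly called approximately 80%, and contrasts using both follow-ups reach 81% to 91%. This stands: a reader might infer that the trial lacks the stated power whatever test is run, and the document does not support that.

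A reader might also infer from the match in Step 1 that the trial will test a group effect averaged over baseline and follow-up, which would dilute any treatment effect. The document does not support that either. No section plans such a test, and 140 fits a group-by-time test with a sustained effect almost as well.

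It can also be said that 122 is a complete-case count. The plan seeks endpoints from withdrawals, imputes missing data and uses mixed models, and people who leave after week 12 still contribute a CogState visit. In addition, the 20% is described as possible and is tied to the muscle calculation. This is partly right: applying it to cognition is an inference, though a natural one for the same participants. Imputation does not replace the information lost with missing endpoints, and endpoints from withdrawals are promised only where possible. With no loss at all, 152 gives 82% on the formula of Step 1 and 86% on the week-24 baseline-adjusted contrast.

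Finally, the per-group figure of 152 would remove the shortfall. It contradicts the total in two other places, so it needs correcting rather than relying upon.

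The choice of d = 0.40, just under the 0.41 to 0.59 that the paragraph cites, is not an error.

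**Conclusion.** The point holds in a limited form and is moderate in severity. The cognitive requirement of 140 has no visible allowance for the protocol's own 20% loss. With 152 in total, about 122 would have endpoint data, and power on the calculation closest to 140 falls from 78% to about 73%. For contrasts that target the treatment effect on change, it lies between about 69% and 91%, depending on which is chosen.

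This rests on 152 being the total, on 20% loss applying equally to cognition, on d = 0.40 at the visits tested, on a correlation of 0.6 between all visits, and on those lost contributing no endpoint information. The muscle calculations are not affected.

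**What to change.** Reword the Sample size calculations section in four places:

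1. Reconcile the per-group figure of 152 with the total of 152 in the Abstract and the Participants section.
2. State that 140 means evaluable participants.
3. Name the treatment contrast that f = 0.20 describes, and give it as d = 0.40 as well. It should be the contrast that the mixed model will test.
4. Restate cognitive power for that contrast at about 122 evaluable. If the sponsor chooses the week-24 baseline-adjusted difference, for example, this is about 78% power for d = 0.40, or a detectable d of about 0.41 at 80% power. The sponsor may choose another contrast; the document does not fix one.

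The cost is rewording and a slightly less favourable power figure under most contrasts. No extra participants are required.

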### Statistical analyses

The primary statistical analysis will be conducted on an intention-to-treat basis using STATA statistical software release 13.0 (STATA, College Station, TX, USA). For participants with at least 66 % compliance to the exercise program (two out of three sessions per week) and 80 % compliance with the lean red meat, per protocol analyses will also be performed. Descriptive statistics will be used to compare the background variables and baseline measures between the groups, and any imbalances will be adjusted for during subsequent analyses. Wherever possible, we will obtain endpoint measures from all withdrawals and include all randomised participants in our final data analysis. Any missing data for participants that are lost to follow-up will be handled with multiple imputation, but sensitivity analysis will be conducted to evaluate the effect of potential non-random attrition. All data will be checked for normality prior to analysis, and data that is skewed will be log transformed prior to analysis. Baseline measures and changes in outcome variables will be presented as means ± SD or 95 % confidence intervals. The effects of the intervention will be assessed using linear mixed models with random effects. Subsequent adjusted analysis for potential covariates (age, sex, race/ethnicity, cardiovascular disease risk, depression/anxiety, changes in medication and change in habitual physical activity or diet) will also be conducted. Multiple regression analysis will be used to investigate whether body composition, circulating neurotrophic, growth or inflammatory markers, bioavailable zinc and cardiovascular risk factors are associated with changes in cognitive function. The significance level will be set at P<0.05 or smaller if adjustments are made for multiple comparisons.

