#### Randomisation and blinding

Randomisation will be at the level of the individual participant in blocks of four, stratified by gender, using a computer-generated random number sequence by an independent researcher. Neither the participants nor research staff involved in the testing will be blinded to the allocation, but those analysing the data will be blinded. A flow diagram of the study protocol is outlined in Fig. 1.

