#### Lean red meat

Participants allocated to the red meat group will be supplied with ~220 g (raw weight) of lean red meat to be consumed on each of the three training days per week for 24 weeks to achieve a modest increase in mean dietary protein intake in mean dietary protein intake to a level of at least 1.3 g/kg/day. This equates to ~160 g of cooked meat per day (~45 g of protein). All participants will be asked to prepare the meals themselves and consume the meat at lunch and dinner (~80 g cooked serving per meal) as there is emerging evidence that a divided dose of protein spread throughout the day may be more effective for enhancing muscle protein synthesis than a single large dose in the evening [49]. The meat will be supplied in labelled 110 g portion packs trimmed of visible fat, and participants will select from a variety of veal, lamb or beef cuts, delivered frozen every 4 weeks by a local butcher. Participants living with a partner will also receive sufficient food supplies for their partner. For the other non-training days, participants will be advised to maintain their usual diet. All participants will be provided with instructions of how to maintain a daily protein rich diet (e.g. foods and recipes rich in protein) and will receive recipes and written dietary instructions for consuming the red meat. We have found that this dietary intervention in older women results in a modest average increase in dietary protein from 1.1 to 1.3 g/kg/day [15]. We therefore expect that participants will achieve an intake of approximately 1.3 g/kg/day for 3 days/week when exercising and around 1.1 g/kg/day for the remaining 4 days.

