##### Compliance

Exercise cards completed by the participants and monitored by the exercise trainers will be used to monitor adherence to the exercise program. Moreover, at each training session the exercise trainers will document attendance/non-attendance for each participant, and will contact the research staff if participants miss multiple sessions consecutively. The exercise cards will be collected by the research staff from each health and fitness centre at approximately monthly intervals throughout the intervention for review. To monitor the consumption of lean red meat, participants will be asked to record all meat products consumed (from that supplied by the investigators) on a compliance calendar, which will be collected every month. Participants in the carbohydrate control group will also be asked to complete a checklist of carbohydrate-rich meals (pasta and rice) on a daily calendar. Compliance with the vitamin D supplements will be checked by counting returned tablets at after 6 months.

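### The per-protocol rule sets a dietary threshold that only the meat arm can meet, so the two arms are selected differently

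*Protocol article*

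**What the plan says.** All references are to the Protocol article.

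- **Statistical analyses.** "The primary statistical analysis will be conducted on an intention-to-treat basis". A per-protocol analysis is added, with two conditions joined by 'and'. The exercise condition is "For participants with at least 66 % compliance to the exercise program (two out of three sessions per week"; the dietary condition is 80% "compliance with the lean red meat, per protocol analyses will also be performed". No other dietary condition is given.
- **Exercise program.** Participants in both arms follow the same supervised training, so the exercise condition can be applied to both.
- **Lean red meat.** "Participants allocated to the red meat group will be supplied with ~220 g (raw weight) of lean red meat". Controls receive none.
- **Compliance.** For meat, "participants will be asked to record all meat products consumed (from that supplied by the investigators) on a compliance calendar". Controls are asked to "complete a checklist of carbohydrate-rich meals (pasta and rice) on a daily calendar".
- **Carbohydrate control.** Controls have their own dietary instruction: at least one serving of rice, pasta or potato on each training day.
- **Table 1.** Compliance with meat and with carbohydrates is one item, recorded on a daily calendar.

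**The concern.** Randomisation protects a comparison of subsets only if selection after randomisation works alike in both arms. Here one arm passes an extra adherence filter. Participants know their allocation and record their own diet, so keeping to the meat schedule could reflect motivation or health as well as the meat itself. If so, the retained meat participants would differ from the retained controls even if meat had no effect, and the per-protocol difference would mix that selection with any benefit of meat.

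The rule also does not say what happens to controls. If it stays as written, someone must decide after data collection whether and how controls enter the set, which leaves the per-protocol result open to challenge.

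**Working it through.** **Step 1. Apply the rule to each arm.**

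| Condition | Meat arm | Control arm |
|---|---|---|
| At least 66% of exercise sessions (two of three is 66.7%) | Applies | Applies |
| 80% of the lean red meat | Applies | No meat supplied and no record of it |
| Control carbohydrate servings | Not relevant | Recorded, but no threshold set |

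With 'and' taken literally, the control column is empty and there is no comparison. If the meat condition is waived for controls, the meat arm has two filters and the control arm one. Neither reading selects the arms alike.

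**Step 2. Illustrate the size.** The plan gives no figure to reproduce.

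- *From Sample size calculations:* SD of change in lean mass 0.9 kg; target difference 0.5 kg.
- *Assumed, not in the document:* 80% meet the exercise rule; a proportion p meets the meat rule; exercise and diet adherence correlate ρ = 0.3; each correlates r = 0.1 to 0.3 with outcome; the scores are normal; the true effect is zero.

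Let a = Φ⁻¹(0.20) = −0.8416, b = Φ⁻¹(1 − p), s = √(1 − ρ²) = 0.9539, and let P be the proportion passing both filters.

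Mean outcome among retained controls, in SD units:
r·φ(a)/0.80 = r × 0.2800/0.80 = 0.350r

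Mean outcome among retained meat participants:
r·[φ(a)Φ((ρa − b)/s) + φ(b)Φ((ρb − a)/s)]/P

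- p = 0.80: r × (0.2800 × 0.7316 + 0.2800 × 0.7316)/0.6661 = 0.615r. Difference 0.265r SD; × 0.9 kg = 0.239r kg.
- p = 0.60: r × (0.2800 × 0.5004 + 0.3863 × 0.7889)/0.5137 = 0.866r. Difference 0.516r SD; × 0.9 kg = 0.464r kg.

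| Meet meat rule | Kept, meat / control | Spurious difference, r = 0.1 to 0.3 | Share of 0.5 kg |
|---|---|---|---|
| 80% | 67% / 80% | 0.02 to 0.07 kg | 5% to 14% |
| 60% | 51% / 80% | 0.05 to 0.14 kg | 9% to 28% |

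A simulation with 1,000,000 per arm agrees to within 0.004 kg. At p = 0.90 the bias is only about 0.01 to 0.04 kg. At r = 0 it is zero for every p.

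**Step 3. Effect on the error rate.** Take 152 in total, as in the Abstract (Sample size calculations says 152 in each group; I use the smaller reading). That is 76 per arm, and 76 × 0.80 ≈ 61 after drop-out. In the worst case above, 61 × 0.5137 = 31.3 meat participants and 61 × 0.80 = 48.8 controls remain. The standard error is 0.9 × √(1/31.3 + 1/48.8) = 0.206 kg and the bias is 0.139/0.206 = 0.68 standard errors. The two-sided type I error is then Φ(−1.96 − 0.68) + Φ(−1.96 + 0.68) ≈ 0.10. In the mildest case (p = 0.80, r = 0.1) it is 0.052.

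**Step 4. Parallel rule.** With a dietary filter of the same strength in both arms, the simulated difference is −0.003 to +0.002 kg, which is simulation error. This assumes that carbohydrate adherence relates to outcome as meat adherence does.

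**The case against.** **The analysis is supplementary.** Intention-to-treat is primary, endpoints are sought from withdrawals, and missing data are imputed with a sensitivity analysis. No primary estimate, sample size or error rate uses this rule. This stands, and it limits the weight of the point.

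**The literal reading is strained.** The authors evidently meant the meat condition for those assigned meat. That is probably so, but this reading is the one that produces unequal selection.

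**Detail by arm belongs in an analysis plan.** Often true. Here, however, the article states the rule with both thresholds, and what it states does not work for one arm.

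Four stronger readings are tempting, and the document does not support them:

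- *Controls are unselected.* They pass the exercise threshold; they are unselected on diet only. A calculation that ignores this shared filter overstates the bias. With r = 0.3 and 70% kept it gives 0.3 × 0.3477/0.70 = 0.149 SD, or 0.134 kg. With the exercise filter included, the same inputs give (0.739 − 0.350) × 0.3 × 0.9 = 0.105 kg.
- *The bias certainly favours meat.* The direction depends on diet adherence being positively related to outcome, which the document does not establish.
- *The meat flag unblinds the analysts.* The plan says "those analysing the data will be blinded", but nowhere says that they would receive a raw meat-compliance variable.
- *The control calendar is collected and never used.* The article lists it for monitoring compliance. It only omits it from the per-protocol rule.

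**A parallel rule may not be truly symmetric.** The control checklist names pasta and rice although potato is allowed, and the article itself notes that all adults eat some carbohydrate daily. One serving per training day may be met almost automatically and so select weakly. This stands and shapes the fix.

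**Conclusion.** The point holds for the supplementary analysis. The rule selects on exercise in both arms and on diet in the meat arm only; taken literally, it leaves no controls. That defect follows from the text and needs no numerical assumption.

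The size does depend on assumptions. Over the inputs listed in the check, the spurious difference is about 0.02 to 0.14 kg in favour of meat, or 5% to 28% of the 0.5 kg target. It vanishes if adherence is unrelated to outcome. The document gives neither the pass rates nor the correlations, so this is an illustration and not a forecast. The primary conclusion is not at risk. The change should be made because it is cheap and is best settled before adherence data are examined.

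**What to change.** Define the per-protocol set by arm, with parallel criteria:

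- both arms: at least 66% of exercise sessions;
- each arm: at least 80% of its assigned training-day servings (meat, or rice/pasta/potato), counted from the compliance calendars.

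Make sure that the control checklist also records potato, so that a control who chose it is not classed as non-adherent. Adjust the per-protocol model for baseline predictors of adherence. Report the result as supportive only, because carbohydrate adherence may not select participants as meat adherence does.

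The cost is a short change to the definition and one added item on the control checklist. The downside is a somewhat smaller per-protocol set, since some controls would now be excluded on diet.

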#### Primary outcome measures

The primary outcome measures will be changes in total body and regional (leg) lean tissue mass and muscle cross-sectional area, muscle strength and cognitive function.

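### Covariates are to be chosen by observed baseline imbalance with no criterion, and the primary mixed model names neither the baseline outcome nor gender, the randomisation stratum

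*Protocol article*

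**What the plan says.** Three statements in the protocol article bear on this point.

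- **Covariate rule (Statistical analyses).** Background variables and baseline measures are compared between the groups, and "any imbalances will be adjusted for during subsequent analyses". The article does not say what counts as an imbalance or which variables are eligible.
- **Effect model (Statistical analyses).** "The effects of the intervention will be assessed using linear mixed models with random effects". The fixed effects are not listed. Sex appears only in the sentence that follows: "Subsequent adjusted analysis for potential covariates (age, sex, race/ethnicity, cardiovascular disease risk" and further items.
- **Design (Randomisation and blinding).** "Randomisation will be at the level of the individual participant in blocks of four, stratified by gender".

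Two other places show how baseline may enter. The Primary outcome measures section defines the outcomes as changes. CogState "will be used to assess cognitive function at baseline, 12 and 24 weeks", whereas Table 1 has lean mass, muscle area, strength and BRIEF-A at baseline and week 24 only.

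**The concern.** The covariate rule is something the article states, not a detail it leaves out. A later analysis plan that fixed the covariates in advance would have to depart from it.

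Under randomisation every baseline imbalance is due to chance, and its size says nothing about whether the variable predicts the outcome. With as many baseline measures as Table 1 lists, some will look unequal by luck and be adjusted for, while strong predictors that happen to be balanced are left out. Because no threshold is given, the model is settled only after the data are seen, and each primary outcome could end with a different covariate set.

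The stratum raises a related issue. The design balances gender, but the analysis does not name it at the primary step. If gender predicts the outcome, leaving it out keeps its variance in the residual, and the standard errors are then generally too large.

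**Working it through.** **Inputs.** From Sample size calculations: f = 0.20, so d = 2f = 0.40; r = 0.6 among repeated measures (cognition only); N = 140; two-sided 0.05; SD of change 0.9 kg (lean mass) and 30% (strength); 20% drop-out. The total of 152 is from the Abstract: 76 per arm, and 76 × 0.8 = 60.8, about 61 completers per arm (N = 122).

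**The plan's own figure.** For the between-group test in a repeated-measures analysis with m measurements, λ = N f² m / (1 + (m − 1) r).
- m = 3: 140 × 0.04 × 3 / 2.2 = 7.64, power 78.4%.
- m = 2: 140 × 0.04 × 2 / 1.6 = 7.00, power 74.8%.

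The stated power of approximately 80% therefore reproduces with three measurements.

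**Variance of the group difference, one follow-up.** With equal variances at both visits, in units of the follow-up-only variance:
- change score: 2(1 − r) = 0.80
- baseline-adjusted: 1 − r² = 0.64
- ratio adjusted to change: (1 − r²) / (2(1 − r)) = (1 + r)/2 = 0.80, a saving of 20%

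With two visits and free baseline means, the group-by-time term of a mixed model is the change-score estimate. With baseline means constrained equal, the model matches baseline adjustment and the saving is already obtained.

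**Power at N = 122.** λ = N f² / v, where v is the relative variance and N f² = 122 × 0.04 = 4.88.
- change: 4.88 / 0.80 = 6.10, power 68.8%
- adjusted: 4.88 / 0.64 = 7.63, power 78.2%

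For 80% power the totals are 160 (change) and 128 (adjusted); 160 / 128 = 1.25 = 1 / 0.80.

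**Dependence on r.** The saving over the change score is (1 − r)/2: 35% at r = 0.3, 25% at 0.5, 20% at 0.6, 10% at 0.8 and 5% at 0.9.

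For lean mass the between-person SD is not given. With equal variances, r = 1 − 0.9² / (2 SD²). Over an assumed range:
- SD 3 kg: r = 0.955, saving about 2%
- SD 5 kg: r = 0.984, saving about 0.8%
- SD 10 kg: r = 0.996, saving about 0.2%

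**The imbalance trigger.** This was simulated with 20,000 trials, 61 per arm and r = 0.6. The trigger was assumed to be a baseline difference in the outcome at p < 0.05, because the article names none.

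| Analysis | Type I error | Power, d = 0.40 |
|---|---|---|
| Always adjust for baseline | 4.9% | 78.3% |
| Change score, adjust if triggered | 4.5% | 69.9% |
| Follow-up only, adjust if triggered | 3.9% | 60.4% |
| Better of change and adjusted | 7.0% | – |

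An unadjusted change score had 69.0% power in the same simulation, so the trigger recovers almost none of the available gain.

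**Gender.** The share of outcome variance due to gender is not given, so the effect of leaving it out cannot be computed.

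**The case against.** The strongest reply is that an article need not list fixed effects, and that baseline is probably in the model already. The outcomes are changes and the power statement assumes correlated repeated measures, so baseline most naturally enters as a repeated measurement. This stands. A reader might infer that the primary model omits the baseline outcome; the article does not say so. For the same reason, the follow-up-only row above describes an analysis that the article does not propose.

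The words about subsequent analyses may refer only to the later adjusted analysis and not to the primary model. The text allows that reading but does not settle it. Under it, the rule would still choose covariates by imbalance, but in a secondary analysis.

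A reader might also infer that the rule inflates the type I error. A mechanical trigger does not: it was slightly conservative. The 7.0% arises only if someone reports the better of two analyses, which the article does not propose, and it says that those analysing the data will be blinded. Nor does leaving out a balanced stratum make the analysis anti-conservative; the error generally runs the other way.

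Finally, r = 0.6 is stated for cognition alone, where CogState has two follow-ups, while the power comparison uses one. Lean mass and strength were powered on change. At 61 per arm, Φ(Δ/σ × √(n/2) − 1.96) gives 86.6% and 91.2%, so neither depends on baseline adjustment to exceed 80%.

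**Conclusion.** The point holds in a limited form. Two features are in the text: covariates are selected by observed imbalance with no criterion, and the stratification factor is named only in a later adjusted analysis. The primary model also does not name adjustment for the baseline outcome, which leaves open whether precision is lost.

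If the baseline means are left free, the loss against baseline adjustment is 20% of variance at r = 0.6, or roughly 69% against 78% power at 61 per arm, d = 0.40 and one follow-up. It is about 5% at r = 0.9, probably less for lean mass, and nil if the baseline means are constrained equal. A general statement that the trial forgoes the equivalent of 25% more participants is not supported, because that figure belongs to r = 0.6 and a change-score analysis. The cost of leaving out gender has a likely direction (standard errors too large) but no computable size.

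This is a weakness worth correcting; it does not invalidate the trial.

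**What to change.** State in advance that the primary model for each primary outcome contains group, time where there is more than one follow-up (CogState at weeks 12 and 24), the baseline value of that outcome, and gender. A mixed model with baseline means constrained equal across the groups, plus gender, serves the same purpose. Delete the sentence that triggers adjustment by imbalance and keep the baseline comparison as description only. Adding recruitment cohort is optional, since it is not a stratification factor.

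The cost is a change of wording. Baseline outcomes and gender are already collected, and no extra visits or participants are needed.
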